#### Sample size estimation

The sample size is calculated based on implementation outcomes of health system adoption, cost, fidelity, penetration, and sustainability.*For power calculation*, we used Power (1 − β) = 0.8 and α = 0.05 and did not assume equal cluster sizes. The coefficient of variation (CV) of cluster sizes is set to 0.2, allowing for a large variability between clusters. Methods from Donner et al. [59] implemented in R for cluster RCTs were used.*For binary outcomes**,* e.g., adoption, we assumed 15% adoption in the control group based on previous study [23]. Table 3 shows the sample size needed to detect increases in implementation outcomes (e.g., adoption) in the intervention arm from 15% to 25–50% with 80% power. We expect to achieve an increase of at least 15%, to 30% or more, for outcomes such as adoption.*For continuous outcomes* such as sustainability/sustainment, we used estimated variance = 1 (standardized), and variance within clusters = 0.95 (assuming a large proportion of individual WLWH variability). For average cluster sizes (sampling frame per facility) ranging from 400 to 600 WLWH, we have greater than 80% power to detect differences in mean scores between the intervention and control arms as small as 1.4. We aim to recruit at least 1,152 patients (288 per site × 4 sites, inclusive of 20% attrition for a minimum sample size of 240 per site) Thus, the sample size for the Intervention Arm is *n* = 576 and Control Arm is *n* = 576.

**Table 3 Tab3:** Power and sample size calculation

Intervention Numeric	Control Numeric	Minimum Sample Size Per Site
0.25	0.15	504
0.30	0.15	240
0.35	0.15	142
0.40	0.15	94
0.45	0.15	67
0.50	0.15	50

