### Statistical analysis plan

Data will be cleaned and reviewed to determine if distributional assumptions are met. If not, scores will be transformed, or appropriate nonparametric methods will be applied. If distributional assumptions are valid, sensitivity analyses (with and without outliers) will be applied. Hypothesis testing will use α = 0.05 (2-tailed). An intent-to-treat analysis will be used to maintain baseline comparability achieved by randomization.

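### Table 3's 80% power does not follow from four sites: one design effect of about 4.07 is applied to every site size, and at the document's only ICC (0.05) power for 15% vs 30% is about 34%, or 15% on 2 df

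*Protocol article*

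**What the plan says.** All of this is in the protocol article, mostly under Sample size estimation.

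- Error rates: "we used Power (1 − β) = 0.8 and α = 0.05". The Statistical analysis plan section adds "Hypothesis testing will use α = 0.05 (2-tailed".
- Cluster sizes: "The coefficient of variation (CV) of cluster sizes is set to 0.2".
- Binary outcomes: "we assumed 15% adoption in the control group based on previous study", and "We expect to achieve an increase of at least 15%, to 30% or more". Table 3 is described as the "sample size needed to detect increases in implementation outcomes (e.g., adoption) in the intervention arm from 15% to 25–50% with 80% power". Its per-site minimums are 504, 240, 142, 94, 67 and 50 for intervention rates of 25%, 30%, 35%, 40%, 45% and 50%. No ICC or cluster size is given for this calculation.
- Continuous outcomes: total variance 1 and "variance within clusters = 0.95 (assuming a large proportion of individual WLWH variability", which implies an ICC of 0.05. Facility sampling frames of 400 to 600 women are said to give more than 80% power for a mean difference of 1.4.
- Recruitment: 288 per site and 1,152 in all, "inclusive of 20% attrition for a minimum sample size of 240 per site".
- The Randomization section allocates four sites, two to each arm.

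**The concern.** In a cluster trial the design effect depends on the number analysed per cluster. With the number of sites fixed at two per arm, asking for more women per site makes the clusters larger and so raises the design effect. A table that varies the per-site number from 50 to 504 under one design effect is internally inconsistent. The 240-per-site row, which sets the size of the trial, may then be far from 80% power.

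Four clusters also leave only 2 degrees of freedom for the between-arm comparison, and a normal critical value ignores this.

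If the 80% statement stands uncorrected, a null result would be read as evidence that implementation support adds nothing, when the design may have had little chance of showing the planned difference.

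**Working it through.** **Inputs.** Two-sided α 0.05, power 0.80, control rate 0.15, CV of cluster size 0.2 and two sites per arm, all stated. ICC = (1 − 0.95)/1 = 0.05, implied by the continuous-outcome variances.

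**1. Reproduce Table 3.** Unpooled n per arm = (1.960 + 0.842)² × [0.15×0.85 + p(1−p)]/(p − 0.15)². For p = 0.30: 7.849 × 0.3375/0.0225 = 117.73. Multiply by a design effect (DE), divide by 2 sites and round up: 117.73 × 4.07/2 = 239.6, giving 240. The same DE gives every other row (third column of the table below). In a search over DE from 1 to 8, only 4.069 to 4.0735 fits all six rows.

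**2. Where 4.07 may come from.** DE = 1 + [(1 + CV²)m − 1] × ICC. With CV 0.2, ICC 0.05 and m = 60: 1 + (62.4 − 1) × 0.05 = 4.07. The value 60 is back-calculated. The pairs m = 119 with ICC 0.025, and m = 592 with ICC 0.005, fit as well.

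**3. Use each row's own site size.** The ICC that the printed size m would need is (2m/n − 1)/(1.04m − 1). For the 240 row: (480/117.73 − 1)/248.6 = 0.0124. The last three columns instead hold the ICC at 0.05.

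| Rate | n per arm | n × 4.07/2 | Printed m | ICC needed | DE at m (ICC 0.05) | Power, normal | Power, 2 df |
|---|---|---|---|---|---|---|---|
| 25% | 247.2 | 503.1 | 504 | 0.0059 | 27.16 | 19% | 10% |
| 30% | 117.7 | 239.6 | 240 | 0.0124 | 13.43 | 34% | 15% |
| 35% | 69.7 | 141.8 | 142 | 0.021 | 8.33 | 50% | 21% |
| 40% | 46.2 | 93.9 | 94 | 0.032 | 5.84 | 65% | 27% |
| 45% | 32.7 | 66.6 | 67 | 0.045 | 4.43 | 77% | 33% |
| 50% | 24.2 | 49.2 | 50 | 0.062 | 3.55 | 86% | 39% |

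**4. The design row in full.** DE = 1 + (1.04×240 − 1) × 0.05 = 13.43. Effective n per arm = 480/13.43 = 35.7, against 117.7 required. SE = √(0.3375/35.7) = 0.0972, and 0.15/0.0972 = 1.544. Normal power = Φ(1.544 − 1.960) = 33.9%. A noncentral t on 2 df (critical value 4.303, noncentrality 1.544) gives 15.4%. A beta-binomial simulation gave 35% and 17%.

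**5. Ceiling at ICC 0.05.** As m grows, effective n per arm tends to 2/(1.04 × 0.05) = 38.5. Power tends to 36% (normal) and 16% (2 df), so extra women at the same four sites do not help.

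**6. Sensitivity to the ICC, 15% vs 30%, 240 per site.**

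| ICC | Normal | 2 df |
|---|---|---|
| 0.05 | 34% | 15% |
| 0.02 | 64% | 27% |
| 0.01 | 86% | 39% |
| 0.005 | 97% | 53% |
| 0.001 | 99.9% | 73% |

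Normal power reaches 80% at an ICC of about 0.012, where 2-df power is about 35%. On 2 df, the intervention rate detectable with 80% power against 15% is about 44% at ICC 0.01 and about 70% at ICC 0.05.

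**7. Attrition.** 240 × 1.2 = 288, but 288 × 0.8 = 230.4, and 240/0.8 = 300. The 288 covers a loss of 48/288 = 16.7%. At 230 per site and ICC 0.05, normal power is 33.8%.

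**The case against.** The strongest reply is that the low figures rest on an ICC the article never assigns to binary outcomes. That is right. The 0.95 appears only under continuous outcomes, and the cluster size of 60 appears nowhere. If the design effect was set from the 400 to 600 sampling frame, with an ICC near 0.005, the DE at 240 per site would be 1 + 248.6 × 0.005 = 2.24. Normal-approximation power would then be about 97%. So a reader should not infer that the authors used 60, or that power simply is 34%. Those are conditional statements.

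A second reply is that mixed models are planned and the degrees-of-freedom method belongs to an analysis plan that is not shown. The article indeed names no 2-df test. Even so, two sites per arm leave 2 between-cluster degrees of freedom, and a printed 80% power claim has to survive that.

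A t multiplier on 2 df could also reproduce the table: (4.303 + 1.061)² = 28.77, which is 3.67 times 7.849, so a DE of 4.07/3.67 = 1.11 fits. That is again one DE for all rows. At 240 per site it would need an ICC of 0.11/248.6, about 0.0004, for which the article gives no basis.

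It is also tempting to read the continuous statement as proof that a 2-df t test was used there, so that the two halves follow different rules. At ICC 0.05 and 400 to 600 per site, a 2-df calculation gives about 84% power at 1.4, and a normal one gives over 99.9%. But 1.4 is stated as a bound with more than 80% power, so it does not identify the method.

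Finally, the 15% vs 50% row does exceed 80% on the normal scale at ICC 0.05, but it does not set the sample size.

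**Conclusion.** The point holds in conditional form. It is certain that one design effect is applied to site sizes from 50 to 504, and that no single ICC makes Table 3 correct. This does not depend on the inferred cluster size of 60.

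The size of the shortfall depends on the unstated binary ICC. If the implied 0.05 carries over, power for the design case is about 34% (normal) or 15% (2 df) instead of 80%. At an ICC of about 0.012 or less the normal figure meets 80%. Once 2 df are respected it does not, even at 0.001.

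The documents do not support the inference that the between-arm comparison must be abandoned as a hypothesis test. They show only that its stated power is wrong. The attrition slip is real but hardly changes power.

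**What to change.** - State the ICC assumed for binary outcomes, with its basis.
- Recompute Table 3 with the design effect at each row's own per-site size and a small-cluster (2 df) reference.
- Replace the claim of 80% power for 15% vs 30% with the actual power and detectable difference for 1,152 women at four sites, over a stated ICC range such as the one tabulated above.
- Separately, restate the attrition allowance as 16.7%, or the analysable minimum as 230 per site.

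The cost is a rewritten sample-size paragraph and table. No extra participants are needed, and the stated power becomes less favourable. If the sponsor wants to keep 80%, only more sites can provide it at the implied ICC: on the normal approximation, 117.73 × 13.43/240 = about 6.6 sites per arm at 240 women each. That would be a design change, not a correction of the text.

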**Methods:**

This study will be conducted in four HIV clinics in Ghana’s Central Region using a three-phase design.

Preparation Phase (Year 1): Use mixed methods, including nominal group techniques with 40–60 stakeholders (WLWH, healthcare providers, policymakers), to prioritize ISS and refine HOPE into HOPE 2.0 or HOPE-inG.

Implementation Phase (Years 2–3): Conduct a hybrid type 2 cluster-randomized controlled trial, comparing HOPE 2.0 + ISS (intervention group) versus HOPE 2.0 alone (control group). A total of 1,152 WLWH and 80 health providers will be enrolled.

Sustainment Phase (Years 3–5): Evaluate the long-term sustainment of HOPE 2.0 and ISS using quantitative and qualitative methods.

Primary outcomes include patient-level screening and treatment uptake (effectiveness) and provider-level implementation metrics (adoption, cost, fidelity, penetration and sustainability). Data sources include surveys, interviews, electronic tracking and fidelity checklists at multiple organizational levels. Cost analyses will employ micro-costing methods, and fidelity will be monitored through structured observations and log sheets.

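### The 20% attrition allowance was added as 240 × 1.2 = 288 per site; a 20% loss from 288 leaves about 230 women, below the plan's own minimum of 240.

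*Protocol article*

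**What the plan says.** All the figures are in the protocol article, Sample size estimation. The section bases the sample size on implementation outcomes such as adoption. For binary outcomes "we assumed 15% adoption in the control group based on previous study", and it expects the intervention arm to reach 30% or more. On error rates, "we used Power (1 − β) = 0.8 and α = 0.05". Table 3 lists the minimum number per site for each intervention rate at 80% power; its row for 0.30 versus 0.15 gives 240.

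The recruitment target follows: "We aim to recruit at least 1,152 patients (288 per site × 4 sites", described as "inclusive of 20% attrition for a minimum sample size of 240 per site". The section then gives 576 women for each arm. The abstract repeats the total: "A total of 1,152 WLWH and 80 health providers will be enrolled". The article states no other attrition rate and no other attrition formula.

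**The concern.** Attrition is a loss from the women recruited. If a fraction *d* is lost and *n* must remain, recruitment has to be *n*/(1 − *d*). The plan appears to have used *n*(1 + *d*), which is always smaller. The recruitment target then does not protect the minimum that it is said to protect, and a reader who takes the sentence at face value will believe that a 20% loss still leaves 240 per site and 80% power.

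The slip is independent of any question about clustering. Whatever minimum per site is finally adopted, inflating it in the same way would leave it short again.

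**Working it through.** **Inputs** (Sample size estimation and Table 3, unless noted)
- Minimum per site: 240 (30% versus 15%)
- Attrition: 20%
- Recruited: 288 per site, 4 sites, 1,152 in total, 576 per arm
- Power 0.80, α = 0.05, two-sided (Statistical analysis plan section: "Hypothesis testing will use α = 0.05 (2-tailed")
- Two sites per arm (Randomization section)
- Intracluster correlation for binary outcomes: not stated

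**1. Reproducing the plan's target**
- 240 × (1 + 0.20) = 288 per site, an exact match
- 288 × 4 = 1,152 and 288 × 2 = 576, both as stated

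**2. What 288 provides**
- Remaining after 20% loss: 288 × 0.80 = 230.4 per site, 9.6 below 240
- Over four sites: 1,152 × 0.80 = 921.6, against 4 × 240 = 960, a shortfall of about 38 women
- Loss that 288 can absorb: 1 − 240/288 = 16.7%

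**3. What a 20% allowance requires**
- 240 / (1 − 0.20) = 300 per site, 600 per arm, 1,200 in total
- That is 12 more per site and 48 more overall than the stated target

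**4. Where the 240 comes from**

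Take a two-sided 5% t-test with 2 degrees of freedom (four sites less two arms), unpooled variance, two sites per arm and an intracluster correlation of zero. With *m* women per site,

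SE = √{[p₁(1 − p₁) + p₂(1 − p₂)] / (2*m*)}, non-centrality = (p₂ − p₁)/SE.

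The smallest *m* giving at least 80% power for intervention rates of 0.25, 0.30, 0.35, 0.40, 0.45 and 0.50 is 504, 240, 142, 94, 67 and 50. All six rows of Table 3 are matched exactly.

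**5. Power for 30% versus 15% under that method**

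The variance term is 0.15 × 0.85 + 0.30 × 0.70 = 0.3375, and the critical value of *t* is 4.303.

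| Women per site | SE | Non-centrality | Power |
|---|---|---|---|
| 240 | √(0.3375/480) = 0.02652 | 5.657 | 80.0% |
| 239 | √(0.3375/478) = 0.02657 | 5.645 | 79.9% |
| 230 | √(0.3375/460) = 0.02709 | 5.538 | 78.7% |

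So 240 has no slack, and the shortfall costs about 1.3 percentage points.

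**6. Sensitivity to clustering (assumed values)**

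With the same 2-df test and the plan's coefficient of variation of 0.2, the variance is multiplied by 1 + {(1 + 0.2²)*m* − 1} × ICC. The power lost between 240 and 230.4 per site is then about 1.1 points at an ICC of 0.001, 0.6 at 0.005 and 0.3 at 0.01.

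**The case against.** The arithmetic is not in dispute; its importance is. Five points can be made.

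- **The effect is very small.** It is 1.3 points of power at most under the Table 3 method, and less once any clustering is allowed. With 230 per site, 80% power is reached at about 30.3% versus 15%, and the plan expects 30% or more. This stands, and it limits the weight of the point.
- **The total is a floor.** The plan says at least 1,152, so more may be enrolled. That is true, but it is the only target given, the per-arm numbers are stated as 576, and the target as stated does not yield 240 after the stated loss.
- **Attrition does not shrink every analysis.** The Outcomes measures section defines screening uptake over all women enrolled and counts non-completers as failures, so that denominator stays at 288. The plan also specifies intention-to-treat analysis and multiple imputation. This stands for uptake. It does not rescue the sentence, because the plan bases the sample size on implementation outcomes and attaches the 20% allowance to it itself.
- **The 80% is fragile anyway.** Table 3 reproduces only with no clustering. At an assumed ICC of 0.001, power under the 2-df test is about 73% at 240 per site and about 79% even at 300. This is fair: recruiting 300 would not by itself secure 80% power. That is a separate and larger matter, and it does not make the attrition statement correct.
- **Multiplying by 1.2 is a common shorthand.** It may be, but the text calls the 20% attrition and describes 288 as including it, so the statement is wrong as written.

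**Conclusion.** The concern holds. The figures 288 recruited, 20% attrition and a minimum of 240 contradict each other, and nothing elsewhere in the article reconciles them. The allowance actually provided is 16.7%. At 20% loss about 230 women per site remain, some 38 short of 960 over the trial.

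The size of the shortfall rests only on the plan's own numbers. The power figures (80.0% falling to 78.7%) rest on the method that reproduces Table 3, including an intracluster correlation of zero that is inferred, not stated. With clustering the loss is smaller in absolute terms, although power is then lower at every one of these sample sizes. This is a minor error in consequence, but one in a figure that recruitment and later reporting will refer to, and it should be corrected.

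**What to change.** Either of two corrections will do.

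1. **Keep 288 per site and restate the allowance.** In Sample size estimation, say that 288 allows for about 16.7% attrition on a minimum of 240, or that 20% attrition would leave about 230 per site. If a power figure is added, label the 78.7% as conditional on the Table 3 method with no clustering. This is a change of wording only; the abstract total of 1,152 and the 576 per arm stay as they are.
2. **Keep the 20% allowance and change the target** to 300 per site, 600 per arm and 1,200 in total, and amend the abstract to match. The cost is 48 more women. The Recruitment section gives a sampling frame of 400–600 per site and says that recruitment is still open, so this remains possible.

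If the minimum of 240 is itself revised to allow for clustering, divide the new minimum by 0.8 to obtain the recruitment target.

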### Randomization

Study sites are the unit of randomization, and all providers and WLWH at a given HIV clinic at each site will be randomized to the same study arm. Using computer-generated numbers with a block of 2, the four study sites will be randomized to one of two arms: two sites in the intervention group and two sites in the control group (Fig. 3).

**Fig. 3 Fig3:**
[figure not shown]
Flow diagram for HOPE-inG study site selection

### Study procedures

#### Intervention arm

Step 1. Providers, i.e., clinicians, patient navigators, and clinic management at intervention sites will receive a) ISS delivered through management support, capacity-building, and social network support, and b) baseline and refresher training on the HOPE implementation plan.Step 2. Clinicians will a) screen and recruit eligible WLWH, and b) implement HOPE 2.0 by delivering 3R messages via WhatsApp to enroll WLWH.Step 3: WLWH will receive a self-sampling kit from clinicians or patient navigators to collect samples.Step 4: WLWH with positive screening tests will follow up for treatment per the WHO screen, triage, and treat cascade (Fig. 4). Patient navigators will support participants to follow up.

**Fig. 4 Fig4:**
[figure not shown]
Schedule of enrollment, interventions, and assessments. ISS: implementation support strategies

#### Control arm

Providers and clinic managers at control sites will receive baseline training on study implementation, but will not receive any ISS or implementation plan training (Table 2). They will, however, be required to follow Steps 2, 3, and 4 described in the intervention arm described above, except for patient navigator support.

